#### Subgroup analyses

For both BUMP 1 and BUMP 2 prespecified subgroups include eligibility for aspirin prescription to prevent pre-eclampsia (as per National Institute for Health and Care Excellence); gestational age at baseline (≤20 weeks vs >20 weeks), parity (0 vs ≥1). In addition, a sensitivity analysis will compare those women with GH that are recruited de novo into BUMP 2 with those that migrate from BUMP 1.

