Box 2Blood pressure during higher risk pregnancy (BUMP 1) inclusion and exclusion criteriaInclusion criteriaParticipant is willing and able to give informed consent for participation in the trial.Pregnant woman, aged 18 years or above between 16+^0^ and 24+^0^ weeks.Able and willing to comply with trial requirements.Willing to allow her general practitioner and consultant, if appropriate, to be notified of participation in the trial.At higher risk for hypertension in pregnancy/pre-eclampsia defined as one or more of the following risk factors:Age 40 years or older.Nulliparity.Pregnancy interval of more than 10 years.Family history of pre-eclampsia.Previous history of pre-eclampsia or gestational hypertension.Body mass index 30 kg/m^2^ or above at booking.Chronic kidney disease.Twin pregnancy.Prepregnancy diabetes (type 1 or 2)Autoimmune disease (eg, systemic lupus erythematosus or antiphospholipid disease).Exclusion criteriaChronic hypertension.

Box 3Blood pressure (BP) during hypertensive pregnancy inclusion and exclusion criteriaInclusion criteriaWomen with chronic hypertension (defined as sustained systolic BP ≥140 mm Hg and/or diastolic BP ≥90 mm Hg, present at booking or before 20 weeks gestation, or receiving antihypertensive treatment outside pregnancy and/or at time of referral), recruited up to 37+^0^ weeks gestation.ORWomen with gestational hypertension after 20 weeks gestation (defined as sustained systolic BP ≥140 mm Hg and/or diastolic BP ≥90 mm Hg), recruited at 20+^0^ to 37+^0^ weeks gestation.ANDParticipant is willing and able to give informed consent for participation in the trial.Woman aged 18 years or above.Willing to allow her general practitioner and consultant, if appropriate, to be notified of participation.Exclusion criteriaAnticipated inpatient admission considered likely to lead to imminent delivery (within the next 48 hours).

**Table 1 T1:** Schedule of interventions and assessments

	Study period (16 weeks to 8 weeks postdelivery)			
Study visit	Trial entry/baseline	Antenatal follow-up	Notes review	Postnatal follow-up
Time point	20±4 weeks gestation	30±3 weeks gestation	40+4 weeks (postdelivery)	40+8 weeks (postdelivery)
Informed consent	X			
Eligibility assessment	X			
Demographics; including age, race, education	X			
Maternal demographics; including gestation, EDD and parity	X			
Patient Questionnaires; including EQ-5D-5L and STAI	X	X		X
Randomisation	X			

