#### BP during hypertensive pregnancy

An ITT analysis will include women recruited to BUMP 1 who become hypertensive and women recruited de novo to BUMP 2 with GH and CH analysed separately. The primary analysis for BUMP 2 will in each case compare BPs between the intervention and control groups. Analysis of the BP outcome will be by means of a linear mixed-effects model, which can accommodate data where participants have repeated measurements, and also accounts for missing data (assuming data are missing at random). Each of a participant’s BP measures will be modelled by means of a linear mixed-effects model, including random effects for participants and assuming an unstructured variance covariance matrix between measurements from the same participant. Time of BP measurement and randomised group, as well as their interaction term, will be included as fixed effects in the model. A fixed effect will also be included for whether the participant was from BUMP 1 or not in the GH analysis. As a sensitivity analysis inclusion from BUMP 1 or not will be tested as a moderator of the treatment effect. By means of appropriate contrasts, the difference in mean BP of participants in the randomised groups from both BUMP 1 and de novo recruitment will be compared.

BP load and area under the curve will be analysed as continuous outcomes by means of a linear regression model, adjusting for whether the participant originated from BUMP 1. Continuous secondary outcomes, such as birth weight and length of stay, will be analysed by means of regression model. Binary secondary outcomes, such as the development of severe hypertension, incidence of complications and incidence of stillbirth, will be analysed by means of a log binominal model.

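### Gestational age at entry is prespecified as an effect modifier only as a split at 20 weeks, which in BUMP 1 would lose about 25% to 35% of the interaction information if the effect is graded and entry is roughly symmetric

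*Protocol article*

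**What the plan says.** The Subgroup analyses section opens with "For both BUMP 1 and BUMP 2 prespecified subgroups include eligibility for aspirin prescription to prevent pre-eclampsia" and goes on to list "gestational age at baseline (≤20 weeks vs >20 weeks" and parity. No continuous form of gestational age is mentioned, and no model or test is named for any subgroup.

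The entry windows are in Boxes 2 and 3 (Participant timeline section):

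- BUMP 1: "between 16+^0^ and 24+^0^ weeks".
- BUMP 2, chronic hypertension: "recruited up to 37+^0^ weeks gestation", with no lower limit stated.
- BUMP 2, gestational hypertension: "recruited at 20+^0^ to 37+^0^ weeks gestation".

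Table 1 lists "Maternal demographics; including gestation, EDD and parity" among the baseline items. In BUMP 2 the analysis section has "women recruited de novo to BUMP 2 with GH and CH analysed separately". The general statistical section says that full analysis plans will be written before the final analysis; they are not shown here.

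**The concern.** Self-monitoring starts after baseline and stops when labour is established or the pregnancy ends, so gestation at entry largely sets the possible monitoring time. Assuming delivery near 40 weeks, a BUMP 1 woman who enters at 16+0 has about 24 weeks and one who enters at 24+0 has about 16. The split treats 16+0 and 20+0 as the same and separates 19+6 from 20+1. In chronic hypertension the upper group pools women with almost 20 possible weeks and women with about 3.

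The authors themselves note, under Strengths and limitations, that late onset of gestational hypertension may make benefit harder to show, so timing of entry is a question of substance here. If the effect rises or falls steadily with entry gestation, a two-group comparison uses only part of the information in the data. A real gradient is then more likely to be reported as no difference between subgroups.

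**Working it through.** **Plan's own figure.** The article states none for subgroup power or information. The one relevant count is the number of women expected to become hypertensive in BUMP 1: 2262 × 0.16 = 361.9, which reproduces the stated 362.

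**Inputs from the article.** The cut is at 20 weeks. Entry is 16 to 24 weeks in BUMP 1 and up to 37 weeks in chronic hypertension. Allocation is 1:1.

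**Assumed.** The shape of the entry distribution, the lower entry limit in chronic hypertension, and a linear interaction.

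**Formula.** Let X be gestational age and D the indicator X > 20. Under 1:1 randomisation with a linear treatment-by-X interaction, the information kept by D relative to X is R² = corr(X, D)². For X uniform with a fraction p above the cut, this reduces to R² = 3p(1 − p). It is exact for a linear model and an approximation for the two parts of the BUMP 1 hurdle model.

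**BUMP 1, 16 to 24 weeks.** The uniform row follows from 3 × 0.5 × 0.5. The other rows come from simulation with 1,000,000 draws.

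| Assumed entry | R² | Loss |
|---|---|---|
| Uniform | 0.750 | 25% |
| Triangular, peak at 20 | 0.667 | 33% |
| Truncated normal, centre 20, SD 1.5 | 0.650 | 35% |
| Truncated normal, centre 21, SD 2 | 0.645 | 36% |
| Truncated normal, centre 18, SD 2 | 0.563 | 44% |
| Truncated normal, centre 17, SD 2 | 0.448 | 55% |
| U-shaped (beta 0.5, 0.5) | 0.811 | 19% |

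If the lower group is read as including women up to 20+6, uniform entry gives R² = 0.71, a loss of 29%.

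**Chronic hypertension, uniform entry up to 37 weeks.**

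- From 8 weeks: p = 17/29 = 0.586, R² = 0.73, loss 27%.
- From 12 weeks: p = 17/25 = 0.680, R² = 0.65, loss 35%.
- From 16 weeks: p = 17/21 = 0.810, R² = 0.46, loss 54%.

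**Other effect shapes, uniform BUMP 1 entry.**

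- Abrupt change at 20 weeks: the split keeps 100% and the linear term 75%.
- No gradient until 20 weeks, then a linear one: scale X to U, uniform on (−1, 1), so the effect follows max(0, U). Its variance is 1/6 − 1/16 = 5/48. The linear term has R² = (1/6)² / (1/3 × 5/48) = 0.80. The split has R² = (1/8)² / (1/4 × 5/48) = 0.60.

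**Power in context.** Take the 90% power that the article states for the BUMP 1 main effect (standardised effect 1.96 + 1.28 = 3.24) and a 50/50 split, which doubles the standard error of the difference between subgroups. An interaction as large as the main effect has power Φ(1.62 − 1.96) = 37% with the split and Φ(1.62/√0.75 − 1.96) = 46% with the continuous term. At half that size the figures are about 13% and 15%.

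**The case against.** The strongest reply has four parts.

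**The cut is reasoned.** Twenty weeks is the midpoint of the BUMP 1 window and the article's own boundary between chronic and gestational hypertension. A cut named in advance also prevents a data-driven one. This stands, and it is a good reason to keep the split for display.

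**The effect may not be linear.** If it jumps at 20 weeks, the split is the better test. This stands for an exact jump. It does not extend to an effect that merely begins after 20 weeks, where the continuous term still does better (0.80 against 0.60).

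**The analysis plan is not shown.** A reader might infer that the trial will test the interaction only after cutting gestation. The article names subgroups and no test, and a continuous analysis may be in the plan. What can be said is that the published prespecification gives only the two-level form.

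**The consequence is small.** Power for this comparison is probably low with either form, and the article claims power only for the primary and some secondary outcomes. This stands.

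Three further inferences are tempting and unsupported:

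- A 25% loss might be equated with dropping 566 of 2262 women (2262 × 0.25 = 565.5). Information on time to detection comes mainly from the 362 or so who become hypertensive, a quarter of whom is about 90.
- A fall in power from 80% to 68% presumes a continuous interaction test with 80% power, which nothing in the article supports.
- Because gestational hypertension is recruited from 20+0, a reader might recast the point as an empty lower group. That group would be nearly empty among women recruited directly, but the gestational hypertension analysis also takes in women from BUMP 1, and the article does not say which baseline counts for them. The point here concerns lost information in BUMP 1 and chronic hypertension.

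**Conclusion.** The point holds as a minor improvement. The article fixes a two-level form for a moderator that is collected at baseline and plausibly acts in a graded way. If the modification is roughly linear, the split loses about 25% (uniform entry) to 35% (bell-shaped entry) of the interaction information in BUMP 1, with 19% to 55% across other assumed shapes. In chronic hypertension it loses about 27% to 54%.

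These figures rest on assumed entry distributions, an assumed lower entry limit for chronic hypertension, and linearity; the article supplies none of them. It also does not state how precisely gestation is recorded, only that it and the estimated delivery date are collected. The split is a defensible prespecified choice rather than an error. The consequence is confined to a secondary, exploratory analysis.

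**What to change.** In the analysis plan, assess the treatment-by-gestational-age interaction with gestational age at baseline as a continuous term: linear, with a spline check for non-linearity. Keep the 20-week split to display estimates.

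The cost is one model term and a sentence of wording, with no new data. The downsides are a slightly harder presentation, which the displayed split eases, and a linearity assumption that has to be checked.

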### Economic evaluation

The economic evaluation component aims to determine whether BP self-monitoring in addition to usual care represents value for money compared with usual care alone in a population of higher risk pregnant women (BUMP 1) and women with a diagnosis of hypertension during pregnancy (BUMP 2). Two separate within-trial cost-effectiveness analyses will be carried out alongside BUMP 1 and BUMP 2. In addition, a decision analytical model will be built to determine the long-term cost-effectiveness of self-monitoring in pregnancy. A UK NHS perspective will be adopted in all analyses.

The within-trial cost–utility analyses will use individual patient-level data with a time horizon up to 2 months following delivery. The main health outcome measure in the economic evaluation will be maternal quality-adjusted life years (QALYs) over the trial period. The calculation of a QALY profile for each woman will be informed using data from the health-related quality of life instrument EQ-5D-5L that will be collected at baseline, 30 weeks gestation and 8 weeks after birth.^16^ A linear change between utility measures at each time period will be assumed when deriving an individual’s QALY profile. Relevant healthcare resource use during the pregnancy for mothers and their fetuses will include antenatal, intrapartum and postnatal care. Antenatal care utilisation will include primary and secondary care visits including hospital admissions. Intrapartum and related postnatal care before primary hospital discharge will include major procedures undertaken, length of stay and transfers for mothers and their babies. Primary and secondary care resource utilisation during the trial will be collected using case note review including routine and additional clinic visits to midwives and general practitioners (GPs). Unit costs will be extracted from primarily national sources.^17–19^ The cost of using an automated monitor along with the telemonitoring system will be estimated and included in the cost analysis of the self-monitoring group in each trial. Mean maternal QALYs and costs (and associated uncertainty) will be estimated parametrically in the intervention and usual care group in each of the trials. If necessary, we will use multiple imputation methods to deal with missing EQ-5D-5L and resource use data over the trial period and will follow current guidance to conduct and report such analysis.^20^

The long-term decision analytical model will include a decision tree to represent women’s pathways up to the first 8 weeks postdelivery and a Markov model representing the history of disease of women with raised BP after that point, using annual cycles. The structure of the model will be based on models identified via a systematic review of previous economic evaluations of hypertensive patients in pregnancy (currently in progress with PROSPERO number: 123881). Observed risk factors, quality of life and healthcare resource utilisation for randomised participants in BUMP 1 and BUMP 2 will be used to inform the characteristics of a hypothetical cohort entering the model for each treatment pathway. Transition probabilities indicating movement across health states will be informed by cardiovascular risk predictions modified using the literature on risk following hypertensive pregnancy. Costs incurred annually in each health state will be obtained from the literature differentiating between acute and chronic disease health states. Health-related quality of life associated with each health state in the model will also be obtained from the literature.

Both the within-trial cost-effectiveness analysis and long-term model will be reported using current reporting standards for economic evaluations.^21^ Mean differences in costs and QALYs between intervention and usual care arms in each trial and the model will be combined to generate an incremental cost-effectiveness ratio (ICER), presented as cost per QALY gained. Uncertainty around ICERs will be handled using CIs (if appropriate) and cost-effectiveness acceptability curves. Uncertainty in the long-term model will be assessed using probabilistic sensitivity analysis. Recent guidance will also be used to report and interpret the results from the decision analytical model.^22^

### Process evaluation (qualitative and quantitative)

Alongside the trial, we will undertake a process evaluation to assess both quantitative (including the outcomes listed in box 1 above) and qualitative aspects. Intervention fidelity will be assessed for women and participating professionals. This will include for the women: examining persistence with self-monitoring and comparing submitted readings and monitor downloads for a subset of women. For the professionals, a staff survey will assess practice in terms of utilisation of self-monitored BP readings during the trial.

In addition to the quantitative process evaluation, a qualitative study will be conducted within the trial to understand how BP self-monitoring in pregnancy is implemented and its acceptability in daily life and routine clinical practice. In-depth interviews will be completed with a sample of participating women in both BUMP 1 and BUMP 2 and healthcare professionals.^23^

Participating women: The study aims to include approximately 40 pregnant women across five sites, including a sample of up to eight women who decide not to take part or discontinue from the intervention and are willing to be interviewed.^24^ The interviews with women will look to understand real-life implementation issues with BP self-monitoring. Women who have consented to contact at main trial enrolment will be contacted by phone/email/in person regarding the interviews and provided with a patient information sheet (PIS); they will be consented separately prior to the start of the interview. Additionally, an ethnographic study will follow a sample of 10–15 women who monitor their BP.^25^ This ethnographic study will include longitudinal interviewing and non-participatory observations to understand in detail how women engage with home monitoring over time and whether and how home BP readings are incorporated into clinical encounters.^26 27^

Healthcare professionals: Interviews will be conducted with 30–40 midwives and obstetricians who are involved in BUMP 1 and BUMP 2.^24^ The aim is to understand how self-monitoring is operationalised in practice and provide key information for the process evaluation.

Detailed field notes will be taken of observations. Interviews will be audio recorded so that content can be transcribed. Data collection and analysis will be guided by theory, including social cognitive theory, a ‘technology in practice’ perspective and normalisation process theory as interpretative frameworks to understand how the trial intervention ‘fits’ within existing practices and systems, and how it becomes embedded (or not) in women’s lives and healthcare professionals’ routine work.^28–31^ Inductive and deductive approaches to categorising and coding the data will be combined, drawing on a priori theoretical concepts (including, g, self-efficacy, unexpected use of technology and cognitive participation) while remaining sensitive to themes that emerge from the data themselves. An iterative analytical process will be employed to map the range of phenomena and identify associations between themes with the aim of illuminating the mechanisms that underpin the outcomes of the intervention.^32^ QSR NVivo will be used to support the organisation and retrieval of the qualitative data.^33^

### Data monitoring

Regular monitoring will be performed by the trial team according to Good Clinical Practice (GCP) and Clinical Trial Unit standard operating procedures. Data will be evaluated for compliance with the protocol and accuracy in relation to source documents. Following written standard operating procedures, the monitors will verify that the clinical trial is conducted and data are generated, documented and reported in compliance with the protocol, GCP and the applicable regulatory requirements.

A trial steering committee (TSC) and data monitoring committee (DMC) will be convened and review trial progress every 6 months. The TSC will provide overall supervision of the trial and ensure its conduct is in accordance with the principles of GCP and the relevant regulations. The TSC will agree the trial protocol and provide advice to the investigators on all aspects of the trial. The TSC will include members who are independent of the investigators, in particular an independent chairperson. The independent DMC will inform the TSC regarding the accruing trial and safety data, to ensure trial site staff and participants are aware of any relevant safety information and to advise the TSC regarding the appropriateness of continuation of the trial. Any consideration of the need for termination of the trial will be on the advice of the DMC and TSC who will consider the need for prospective criteria for termination.

### Harms/potential risks

During these randomised controlled trials, participants will continue to receive ‘usual care’ regardless of randomisation group, and thus we anticipate that the potential risks are low. Particular issues include the possibility of increased anxiety due to the study. Training of participants will cover repeated measurements in the case of unusually high or low readings. The participant guideline/booklet will give clear advice to women to contact the antenatal care team or other healthcare professional (eg, GP) in the case of persistent high or low readings. The telemonitoring system will automatically provide this advice when high or low readings are sent in. Women will continue to be seen by their clinical teams (midwives/GPs/obstetricians) at frequencies chosen by their clinicians throughout, regardless of randomisation group.

Participants will be advised to seek immediate medical help if they experience any symptoms of pre-eclampsia, regardless of their BP readings.

It is not anticipated that the study intervention (self-monitoring of BP) should result in any AEs but collection of such events will be included in case such events occur so that they can be considered for causal links to the study. Only AEs that are clinically judged (by the supervising site principal investigator) as being caused by the trial intervention will be reported to the Clinical Trials Unit to raise appropriately to the sponsor/Research Ethics Committee that gave favourable opinion. In addition, any maternal death or stroke, fetal loss or neonatal death will be reported to the DMC regardless as to whether they are judged related. Side effects as stated in the British National Formulary will not be reported as AEs.

## Ethics and dissemination

### Ethics approval and consent to participate

Any subsequent protocol amendments will be agreed with both sponsor and ethics committee prior to implementation. The study sponsor reviewed and ensured all indemnity and insurance requirements for the trial were in place prior to the start of recruitment which would operate in the event of any participant suffering harm as a result of their involvement in the research. NHS indemnity operates in respect of the clinical treatment that is provided. Participants will provide written informed consent prior to enrolment. An independent trial steering group will monitor study progress assisted by an independent DMC and will periodically review the study.

